**Table 3 T3:**
[figure not shown]
The blind method assessment questionnaire.

The blind method assessment questionnaire is shown in Table 3.

### Statistical analysis

4.6

The intention-to-treat (ITT) analysis will be used in this study. Data analyses will be performed with the use of the statistical software of SPSS version 23.0. The generalized linear mixed model will be used to compare primary and secondary outcomes between groups and test correlation between baseline factors, and the primary and secondary outcomes. All statistical tests will be two-sided, and *P* < .05 is considered statistically significant.

### Monitoring

4.7

According to recommendation of the National Institutes of Health (NIH), this trial established an independent Data and Safety Monitoring Board (DSMB). The committee consists of 3 members, including an acupuncturist, an endocrinologist, and a statistician. The committee will supervises whether the study follows the protocol design and standard guidelines, will monitor the progress of the trial, and will observe whether adverse events and etiologies are adequately recorded. This DSMB also identify problems in the project, if any; the committee will make the decisions to change the details of this protocol and announce the research personnel by written notice after approval by the ethics committee. Moreover, a qualified clinical trial expert will be invited to monitor this trial and the PI will take full responsibility and make the final decision.

### Ethics approval and consent to participate

4.8

This trial was approved by the Ethics Committee of Chengdu University of Traditional Chinese Medicine. Written informed consent will be obtained from all participants prior to enrolment in the study. This RCT will be undertaken according to the ICH-GCP Guidelines. The latest version of this protocol is 1.1, dated 15 December 2019.

### Availability of data and materials

4.9

All data will be available from the 6th month to the 3rd year after completed and published. For reasonable data requests please contact the corresponding author.

## Discussion

5

Diabetes mellitus has reached epidemic proportions worldwide, and DNB is a frequent complication related to the duration of diabetes, with a reported incidence ranging from 25% to 87%.^[33]^ These DNB patients may be asymptomatic or have a variety of urinary symptoms, such as overactive bladder and urgency incontinence, resulting in decreased bladder sensation and overflow urinary incontinence.^[34]^ The symptoms of DNB were described as diminished bladder sensation, poor contractility in previous. DNB is currently considered to be a progressive disease including a broad spectrum of lower urinary tract symptoms such as urinary urgency, frequency, incontinence, and nocturia. Although DNB seriously affects the quality of life and threatens the psychological and physical health of individuals, it has received less attention. Usually, DNB patients have reached the advanced stages when they consult a doctor.

To evaluate the effect of urinary incontinence, the bladder diary (safe and convenient, various language version) are recommended by the ICS. The severity of DNB is mainly relied on patient-reported outcomes, and 72 hours voiding diary is widely used as an outcome measure in bladder dysfunction studies. AUA-SI has been validated for patient lower urinary tract symptoms and has now applied to bladder dysfunctions (urgency, frequency, incontinence and nocturia).^[22]^ The diabetic neuropathy can produce voiding dysfunction. And the most reliable examination in patients with a voiding dysfunction is measuring the PVR.^[35]^ Relevant animal and clinical studies show that urodynamic test is an appropriate method to study urinary function.^[36]^ The prevalence of bladder dysfunction diagnosed using urodynamics tests can range from 25% to 90%.^[22]^ Several studies suggest that urodynamic tests could accurately diagnose the underlying pathology in bladder dysfunction.^[37]^

As a feasible complementary and alternative therapy, acupuncture has been widely used in clinical practice in many countries for the treatment of bladder dysfunction and improve neurological functions.^[19]^ In addition, acupuncture is gradually gaining acceptance in urology as an effective treatment for lower urinary tract symptoms.^[38]^ Alpha-lipoic acid (ALA) and methylcobalamin (MC) could improve the signs of diabetic neuropathy by enhancing the metabolism and antioxidant capacity of nerve and vascular endothelial cells.^[39]^ Therefore, MC and ALA are usually selected as clinical basic treatment medicine for DNB. Our study protocol is based on the previous clinical experience and relevant clinic reports. However, this protocol still faces some challenges. The first is the sensitivity of urodynamic test. The urodynamic examination is an invasive test that is influenced by patient emotion environmental factors. The second is the blinding method. The nature of the clinical acupuncture therapy made double-blinding impossible. However, this study still has several strengths. The first innovation of this protocol is use of the CTRS to evaluate patients’ credibility of acupuncture treatment and its impact on acupuncture treatment. Moreover, this is the first study to analyze the curative effect of acupuncture on DNB buy using the objective tools (trans-abdominal ultrasound and multi-channel urodynamics) and subjective method (AUA-SI scale and 72h-BD).

This trial should provide us with information on the effect of treating DNB patients with only EA, western medicine or as a combination of both. The additive effect or synergistic effect of acupuncture and western medicine will then be analyzed. We expect that this trial will advance knowledge on the acupuncture in the treatment of DNB. If the further results confirm that acupuncture therapy is an effective and safe option for DNB, it can be used as a priority treatment in clinical practice.

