**Method/design::**

This is a sham-controlled, patient-blinded, pioneer randomized controlled trial (RCT). One hundred fifty eligible patients will be randomly divided into 3 groups: A. basic western medicine (BWC), B. EA with BWC, C. sham EA with BWC. EA treatment will be given twice a week for 12 weeks at bilateral BL23, BL32, BL33, and BL35. The BWC group will received Alpha-lipoic acid (ALA) and methylcobalamin (MC) treatment for 12 weeks, 2 treatment sessions per week. The primary outcome is scored by the 72-hour bladder diary (72h-BD). The secondary outcomes will be scored by the American Urological Association symptom index (AUA-SI), Post-void residual urine volume (PVR) and urodynamic tests. All the assessments will be conducted at baseline and the 12th weeks after the intervention starts. The follow-up assessments will be performed with 72h-BD and AUA-SI in the 4th, 12th, and 24th weeks after intervention ends.

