### Study design

2.3

We propose a single-center, single-blind, randomized, sham-controlled clinical trial to evaluate the efficacy and safety of EA for neurogenic bladder dysfunction in patients with diabetes mellitus. The trial will be performed at the Hospital of Chengdu University of Traditional Chinese Medicine after ethical approval has been obtained from the Institutional Review Board. A total of 150 eligible patients who meet inclusion criteria will be recruited and randomly divided into the acupuncture group (n = 50), sham acupuncture group (n = 50) and the basic treatment group (n = 50) in a 1:1:1 allocation ratio. After 1 week of washout period, patients will accept 12 weeks of intervention, all treatment will be given twice a week. And the follow-up assessments will be performed in the 4th, 12th, and 24th weeks after intervention ends. The primary outcome will be assessed using the 72h-BD. The secondary outcomes will be measured using the American Urological Association symptom index (AUA-SI) and the PVR, and the urodynamic study. All the assessments will be conducted at baseline, and at the 12th weeks after the intervention starts. The follow-up assessments will be performed with 72h-BD and AUA-SI in the 4th, 12th, and 24th weeks after intervention ends. All participants will sign the informed consent before proceeding with the trial.

The flow chart of the study process is as follows in Figure 1.

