### Randomization, allocation, and blinding

2.8

The central randomization method will be performed by the Chengdu University of Traditional Chinese Medicine. Block randomization will be used, and the block size will be unknown to the principal investigator (PI) and research personnel. The information of participants will be sent by an independent statistician to the center via the hospital's website. Randomization will be performed automatically under the control of a central computer system. The researcher will be able to get the random numbers and group allocation immediately in the form of an email or short message service. Participants will be randomly divided into 3 groups with the ratio of 1:1:1.

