### Adverse events

4.3

Acupuncture is generally considered to be a safe treatment.^[30]^ However, any discomfort or symptoms will be assessed. All details of adverse events will be recorded in the case report forms during the trial. The research personnel will interview patients and complete the adverse event report after the treatment. The DSMB and ethics committee will assess any correlation between the adverse event and the intervention, and make a decision on whether the study should proceed. All treatment related adverse are recorded and compared among groups for the purpose of analyzing the safety of EA treatment.

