### Assessment of blinding

4.5

After the treatment session in weeks 12, the patients will be asked to fill in a questionnaire (Table 3). The percentage of patients from each group who believe that they received a true acupuncture treatment will be the principal standard for measuring the subject blinding success rate. We will analyze the difference in the patients blinding success rates among groups.

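### The safety comparison is worded for treatment-related events only, and difficulty in blinding the acupuncturist is no reason to leave outcome and adverse-event assessors unmasked

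*Protocol article*

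**What the plan says.** **Safety (section 4.3).** Collection is broad: "All details of adverse events will be recorded in the case report forms during the trial". Research personnel interview patients and complete the report after treatment. The DSMB and the ethics committee then judge whether an event is linked to the intervention. The comparison is worded more narrowly: "All treatment related adverse are recorded and compared among groups for the purpose of analyzing the safety of EA treatment".

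**Blinding.** The abstract calls the trial patient-blinded, and section 2.3 says: "We propose a single-center, single-blind, randomized, sham-controlled clinical trial". Section 2.8 has blinding in its title, but the only concealment it describes is that of the block size. On who learns the group it says: "The researcher will be able to get the random numbers and group allocation immediately in the form of an email or short message service". Section 4.5 tests blinding in patients alone: "We will analyze the difference in the patients blinding success rates among groups". The Discussion lists blinding among the challenges: "The nature of the clinical acupuncture therapy made double-blinding impossible".

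**Outcomes.** The primary outcome is the frequency of incontinence episodes from the 72-hour bladder diary (section 4.1). AUA-SI, PVR by ultrasound and multi-channel urodynamics are secondary (section 4.2). Objective 2 in section 2.2 compares electroacupuncture (EA) with sham EA on PVR and urodynamics.

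**The concern.** Randomisation makes the arms comparable for the occurrence of events. It does not make them comparable for a later opinion about what caused each event. A safety comparison limited to related events can hide an excess if events in one arm are more readily dismissed, or create one if the same symptom is blamed on needles where needles were used and on nothing where they were not. The Discussion expects the trial to support calling EA effective and safe, so this comparison carries weight.

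The masking issue is similar. The article presents ultrasound and urodynamics as its objective tools. Their value against a patient-reported primary outcome depends on the operator not knowing the group. The Discussion itself says that urodynamic testing responds to the patient's emotional state and to the environment, so the conduct of the test can matter.

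**Working it through.** No figure in the plan depends on this point, so there is none to reproduce. The check sets the passages side by side, then adds one illustration on assumed values.

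**1. What is recorded against what is compared (section 4.3).** Recorded: all adverse events, in all three arms. Compared: events judged related to treatment. The gap lies in the comparison, not in the data.

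**2. Why the filter matters.** For a given type of event in arm j, let p_j be the probability that it occurs and r_j the probability that it is judged related once it has occurred. The compared quantity is p_j × r_j. Between arms B and A the ratio is (p_B / p_A) × (r_B / r_A). If the true risks are equal, p_B = p_A and the ratio reduces to r_B / r_A, which is purely a difference in attribution. Comparing all events sets r = 1 in every arm and leaves p_B / p_A.

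**3. Whether r can be expected to be equal.**
- Group A has the intravenous medicines and no needles (section 3.1).
- Group B has penetrating needles with current, plus the same medicines (section 3.2).
- Group C has a non-penetrating placebo needle without current, plus the same medicines (section 3.3).

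A local symptom in the lumbosacral area therefore has a needle to be blamed on in B, a placebo device in C, and neither in A. Section 4.3 states no masking for those who interview or those who judge relatedness. The documents give no values for r_j, so neither the direction nor the size of the distortion can be derived.

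**4. Which roles the blinding remark covers.**

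| Role | Does the nature of acupuncture prevent masking? | What the article states |
|---|---|---|
| Patient | No, for EA against sham EA | Blinded |
| Acupuncturist | Yes | Not blinded |
| PVR and urodynamic operators | No, if they do not treat | Nothing |
| Adverse-event interviewers | No, if they do not treat | Nothing |

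Section 2.8 sends the allocation to an unspecified researcher and does not separate that person from the assessors.

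**5. Illustration on assumed values.** With 50 per group and 20% dropout, 50 × 0.8 = 40 are evaluable per arm. Suppose assessment shifts one arm by b standard deviations on a staff-measured outcome when there is no true difference. The standard error of the standardised difference is √(2/40) = 0.2236. The rejection probability of a two-sided 5% test is 1 − Φ(1.96 − b/0.2236) + Φ(−1.96 − b/0.2236).

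| Assumed b | b/0.2236 | Rejection probability |
|---|---|---|
| 0 | 0 | 5.0% |
| 0.1 | 0.447 | 7.3% |
| 0.2 | 0.894 | 14.6% |
| 0.3 | 1.342 | 26.9% |

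The shifts are assumptions and have no source in the document. They show only that a modest shift would matter at this sample size.

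**The case against.** **On masking,** the opposing case is strong. No sentence says that operators, interviewers or analyst know the allocation. The document is a condensed article of a protocol (version 1.1) that is not shown. Calling a trial single-blind describes the patient and does not exclude masked assessors. The Discussion's remark most naturally means that patient and acupuncturist cannot both be blinded, which is correct. The researcher who receives the allocation may simply be the person who delivers treatment. All of this stands. A reader might infer that the assessors are unmasked, or that the article offers the nature of acupuncture as its reason for that; the text supports neither. Masking of the analyst is commonly settled in the statistical analysis plan and is not raised here.

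**On reach,** the primary diary is kept by the patient and AUA-SI is patient-reported, so assessor masking protects them little. PVR relies on the ultrasound machine's own volume calculation (section 4.2.2), and urodynamic diagnoses follow International Continence Society criteria (section 4.2.3). Both limit operator influence without removing it.

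**On safety,** it can be said that all events are recorded in every arm, that a full tabulation could appear in a plan not shown, and that the DSMB is independent. A reader might infer that unrelated events go unrecorded, or that group A can have no related events. Both are wrong: section 4.3 records everything, and an event in group A can be related to the intravenous medicines. What does not fall away is that the one comparison section 4.3 states is worded for related events. Independence of the DSMB is also not masking.

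**Conclusion.** The safety part rests on the text. As worded, section 4.3 compares a subset of events chosen by a post-randomisation judgement with no stated masking, in a design where the arms differ in whether there is a needle to blame. This affects the safety comparison across all 150 patients and should be changed.

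The masking part is an inference from what the article declares: blinding at patient level only, allocation sent to an unspecified researcher, and blinding tested only in patients. It holds in a limited form: inability to blind the acupuncturist is no reason to leave PVR and urodynamic operators or adverse-event interviewers unmasked, and section 2.8 should say how they are kept from the allocation. It concerns mainly the objective secondary outcomes and safety, and does not put the primary outcome in doubt.

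Neither bias can be sized from the document. A reader might expect masking to remove it altogether. It would only reduce it: patients may disclose their group, some urodynamic readings depend on what the patient reports, and group A patients, who have no needling, can know that they are not in an acupuncture arm.

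**What to change.** **Section 4.3.** State that all adverse events (any, serious, and by type) are compared among the three groups regardless of attribution, with treatment-related events in a supplementary table. The data are already in the case report forms, so this costs wording and one more table.

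**Section 2.8.** State that the allocation message goes only to the treating acupuncturist and to staff who need it to deliver treatment. Keep it from existing staff who measure PVR and urodynamics or collect adverse events, where those staff do not treat. The article does not say who does this work, so the sponsor should confirm that the roles are separate. If they are, no new staff or procedure is needed, and the downside is a small logistical burden in keeping the message from assessors. If such masking is already in place, one sentence saying so is enough.

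**Discussion.** Limit the remark on double-blinding to the acupuncturist.

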## Trial status

6

This trial will start recruiting participants in June 2020, and will be completed by 31 December 2022.
